### Power Calculation

Power calculations were conducted with G*Power (version 3.1.9.3) using data collected from the Physical Activity in Rheumatoid Arthritis (PARA) randomised controlled trial (Trial Number: ISRCTN04121489). In the PARA study, accelerometers were utilised to measure SB, LPA and MVPA in a subsample of RA participants, and high-sensitivity CRP was measured as a biomarker of systemic inflammation. Cross-sectional accelerometer data were available for n = 61 participants. A priori power calculation from this data indicated that a sample size of n = 125 would be sufficient to detect statistically significant relationships (power = 0.80, α error of probability = .05), between daily SB and LPA with high-sensitivity CRP (a key inflammatory biomarker in RA).

To ensure the robustness of our calculations for detecting significant changes in broader RA outcomes, we also conducted power calculations for physical function, overall cardiovascular risk score and vitality. For this, cross-sectional accelerometer data, Health Assessment Questionnaire scores (physical function), QRisk-2 scores (cardiovascular risk), and vitality scores (vitality) were available for n = 61, n = 61 and n = 59 participants respectively. A priori power calculation confirmed minimum sample sizes of n = 82 (physical function), n = 14 (QRisk-2) and n = 114 (vitality), would ensure adequate statistical power (power = 0.80, α error of probability = .05) to detect the hypothesised associations.

### Statistical Analyses

SPSS (version 24) will be used to compute descriptive statistics for all measured variables. These will include information regarding participant characteristics (e.g., gender, mean age, ethnicity), health outcomes (e.g., DAS-28, BMI), determinants (e.g., quality of motivation, self-efficacy), as well as levels of SB and LPA among the RA sample. Missing value analyses will be conducted via multiple imputation^92^ or expectation maximization^93^ methods in SPSS, where missing data does not exceed 5%.

Cross-sectional associations between RA participants’ objectively-assessed SB patterns and LPA, with health outcomes (Aim 1) and proposed determinants (Aim 2) will be examined using correlation and regression analyses. Longitudinal associations from baseline (Time 1) to 6-month follow-up (Time 2) will be analysed using regression models.

*Aim 1.* For cross-sectional analyses, objectively-assessed SB patterns and LPA will be independent variables. Dependent variables will include biomarkers of inflammation, disease activity, CVD risk, pain, fatigue, physical function, depression, anxiety, vitality, satisfaction with life, positive and negative affect, and quality of life. For longitudinal analyses, regression models will examine if changes in objectively-assessed SB patterns significantly predict change in health outcomes from baseline (Time 1) to 6-month follow-up (Time 2). Health outcomes will be examined in separate regression models, but analyses will be adjusted for other factors which may influence these associations, as appropriate (e.g., disease duration, age, gender, current medication, and GT3X and activPAL3^μTM^ wear time).

*Aim 2.* For cross-sectional analyses, the determinants of SB in RA (e.g., autonomy support and self-efficacy for physical activity, reducing SB and breaking up SB) will be independent variables, and objectively-assessed SB patterns and LPA in RA will be dependent variables. For longitudinal analyses, regression models will examine if changes in hypothesised determinants of SB and LPA (e.g., autonomy support for reducing SB) significantly predicts change in objectively-assessed SB patterns and LPA from baseline (Time 1) to 6-month follow-up (Time 2). As above, all analyses will be adjusted for potential confounders (e.g., 7-day pain and fatigue [to consider the possibility of bi-directional relationships], GT3X and activPAL3^μTM^ wear time).

Subsequent analyses will use AMOS (version 24) to conduct path analyses and structural equation modelling, in order to examine multivariate relationships and hypothesised process models. For example, psychological processes (e.g., autonomy support for reducing SB) proposed to underlie objectively-assessed accumulated sedentary time and LPA engagement, in turn influencing RA disease outcomes (e.g., DAS-28) will be explored.^37,45,94,95^

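### Expectation maximization is offered as an equal alternative to multiple imputation for data that feed regressions; analysed as one filled-in file, it makes standard errors too small and lifts the 5% false-positive rate to roughly 5–11%

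*Protocol article*

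**What the plan says.** In the protocol article, Statistical Analyses, the missing-data statement is one sentence: "Missing value analyses will be conducted via multiple imputation^92^ or expectation maximization^93^ methods in SPSS, where missing data does not exceed 5" per cent. It expresses no preference between the two methods and mentions no variance correction. It does not say whether the 5% applies per variable, per participant, per time point or over all cells.

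The same section then says what the data are for. Cross-sectional associations under both aims "will be examined using correlation and regression analyses". For the longitudinal part of Aim 1, "regression models will examine if changes in objectively-assessed SB patterns significantly predict change in health outcomes" over six months, and Aim 2 has the same structure with determinants as predictors. The Power Calculation section works at "power = 0.80, α error of probability = .05), between daily SB and LPA with high-sensitivity CRP", so .05 is the level at which the study intends to operate.

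**The concern.** Multiple imputation and EM fill-in are not interchangeable when the next step is a regression. Multiple imputation adds residual noise to each filled value and carries the between-imputation variance into the standard error. A single EM-completed file does neither. Each gap is set to its conditional mean, and the regression then counts that value as an observed one. Residual variance is understated and the effective sample size overstated, so intervals are too narrow and p-values too small.

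At stake is the error rate of the associations the study will report. The longitudinal models of both aims are framed as tests of significant prediction. Each uses four measurements (two variables at two time points), so each has four places where a gap can be filled. Aim 1 alone lists more than a dozen dependent variables in separate models, so any inflation recurs across many tests.

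**Working it through.** **Inputs.** From the article: the two methods and the 5% ceiling (Statistical Analyses); n = 125, α = .05 and power 0.80 (Power Calculation). Assumed: two-sided tests; five covariates, suggested by the examples of adjustment factors; gaps missing completely at random; independent normal variables, apart from a baseline-to-follow-up correlation ρ of 0.5, 0.7 or 0.9 in the change models; EM used to produce one conditional-mean file.

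**The plan's own figure.** The article states no false-positive rate for either method, so there is none to reproduce. Its n = 125 comes without an effect size and can only be inverted. From n = ((1.960 + 0.842)/atanh r)² + 3, atanh r = 2.802/√122 = 0.254, so r = 0.248. This does not bear on the point; 125 serves only as the sample size.

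**Analytic approximation.** Suppose only the outcome has gaps and a share s of rows is complete. The filled outcomes lie on the fitted line, so the slope and residual sum of squares are those of the complete rows. The software, however, divides by the full n twice: once in the residual variance and once through the spread of the exposure. The variance is therefore too small by about s², and naive SE / true SE ≈ s. Hence

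false-positive rate ≈ 2 × [1 − Φ(1.96 × s)]

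- Outcome only, s = 0.95: 2 × [1 − Φ(1.862)] = 6.3%.
- Outcome and exposure with independent gaps, s = 0.95² = 0.9025: 2 × [1 − Φ(1.769)] = 7.7%.
- All four measurements of a change-on-change model, s = 0.95⁴ = 0.8145: 2 × [1 − Φ(1.596)] = 11.0%. This treats a change score with one missing component as carrying no information, so it is towards the upper end.

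**Simulation.** n = 125, true effect zero, EM fill-in, ordinary least squares, nominal 5%. The first three rows used 20,000 replicates each, with 6 of 125 values missing per affected measurement. At 7.6% the Monte Carlo SE is √(0.076 × 0.924/20,000) = 0.2 percentage points.

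| What is missing (5% each) | False positives, EM file |
|---|---|
| Outcome only, cross-sectional | 6.2% |
| Outcome and exposure, cross-sectional | 7.6% |
| Change-on-change, all four measurements independently, ρ = 0.5 / 0.7 / 0.9 | 9.1% / 10.0% / 10.7% |
| Change-on-change, outcome and exposure at follow-up only, different people | 6.8–7.8% |
| Change-on-change, follow-up outcome only | 5.4–6.2% |
| Change-on-change, same people lose both follow-up values | 5.2–6.0% |

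The ratio of naive to true SE was about 0.94–0.95 in the first row, 0.90 in the second and 0.82–0.88 in the third. Smaller separate runs agree in direction. For outcome and exposure they ranged from 6.6% (1,500 runs) to 8.4% (4,000 runs). The 1,500-run set also gave 6.3% for outcome only, 9.8% for change-on-change with four independent gaps and 5.5% when the same people are lost.

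**Comparator.** Multiple imputation (10 imputations, Rubin's rules, small-sample degrees of freedom) was run beside EM on the same 2,000 replicates per scenario. The Monte Carlo SE near 5% is √(0.05 × 0.95/2,000) = 0.5 points.

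- Outcome and exposure each 5% missing: multiple imputation 4.4%, EM 6.7%.
- Change-on-change, four measurements 5% missing, ρ = 0.7: multiple imputation 5.2%, EM 9.0%.

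**The case against.** The strongest reply is that the faulty use is inferred. The article does not say that EM will produce one completed file, that this file feeds the regressions, or which variables it covers. A journal article condenses such detail, and a rule for choosing between the methods may sit in the full protocol or analysis plan. This stands as a limit: the size given here is conditional on that use, and the absence of a selection rule is not itself a fault. It does not remove the point, because the article positively names EM as an acceptable route for data bound for regression.

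The second reply is that a 5% ceiling keeps the bias small. That is largely right. If gaps are at item level within a questionnaire and EM fills them before scoring, the rate is close to nominal: one 4,000-run simulation of a seven-item scale, with an assumed inter-item loading, gave 5.7%.

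Four stronger readings are tempting but not supported:

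- **One fixed inflation, such as 8–9%.** The rate depends on which measurements are missing, and the article does not define the 5%.
- **Much larger inflation, by taking 5% over all cells and concentrating the gaps in a few variables.** That needs missingness on outcome and exposure well above the stated limit, and nothing in the article says this is meant.
- **EM is worse than deleting incomplete rows.** Complete-case analysis does hold the level here, but only type I error under data missing completely at random was compared, not bias under other mechanisms or power.
- **The fault extends to every analysis.** The language of significant prediction appears only for the longitudinal models, and the paragraph on path and structural equation models states no missing-data method.

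**Conclusion.** The point holds, at modest size. The article treats as equivalent two methods of which one, in its usual form, does not give valid standard errors for the regressions planned. At n = 125 and 5% missing, a single EM-completed file gives false-positive rates of roughly 5–11% instead of 5%, with the top of that range in the study's own change-on-change models. Multiple imputation stayed near 5% where the two were compared.

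This rests on the assumptions listed above, chiefly one conditional-mean file analysed as observed and gaps missing completely at random. The simulated variables were also largely unrelated. If the other variables predict the missing values well, the filled values lose less information and the inflation would be smaller. The direction of the error was the same in every layout examined.

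**What to change.** In Statistical Analyses, remove *or expectation maximization* for any analysis that yields a standard error, interval or p-value, and state that the regressions use multiple imputation with results pooled by Rubin's rules. EM may be kept for descriptive means. It would help to say in the same sentence what the 5% is measured on, since the size of the effect depends on it.

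The cost is one phrase and slightly wider, correctly sized intervals. Multiple imputation is already named and available in the same software, and no further data or participants are needed.

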### Protocol

This study will adopt a longitudinal design. Participants will be asked to visit the hospital at 2 time points; baseline (Time 1) and 6-month follow-up (Time 2). At each time point, participants will be asked to undertake 2 visits (i.e., visits 1 and 2) separated by a 7-day period. Specific protocols to be followed are described below.

#### Visit 1

Participants will visit the hospital to undertake physical assessments and complete questionnaires. At the end of Visit 1, participants will be fitted with the ActiGraph (GT3X) accelerometer and activPAL3^μTM^ posture sensor to wear for the subsequent 7 days. The researcher will give verbal and written instructions, plus a demonstration, regarding how to wear each device. Participants will also be given the Bouchard Physical Activity Record (BAR)^66^ to complete on 3 of the days during which they wear the GT3X and activPAL3^μTM^.

#### Visit 2

After 7 days, participants will re-visit the hospital to provide a fasted blood sample, and return the GT3X accelerometer, activPAL3^μTM^ posture sensor and BAR to the researcher. During this visit, they will also be asked to complete questionnaires with specific reference to their experiences of pain and fatigue over the previous 7 days.

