*Actigraph GT3X.* The GT3X triaxial accelerometer (27g; 3.8cm × 3.7cm × 1.8cm) will be attached to an adjustable elastic belt and worn on the right hip in a vertical position.^70–74^ Participants will be asked to remove the device only for sleeping and water-based activities (e.g., swimming, bathing), and to record all replacement/removal in wear time logbooks provided. The GT3X will record accelerations in 1-second epochs, which will be converted into activity counts. These counts will then be interpreted to determine the frequency, intensity and duration of SB and physical activity.

Data collected by the GT3X will be cleaned and analysed using Actilife Software (version 6). For inclusion in analyses, participants will be required to have worn the GT3X for ≥4 days, for ≥10 hours per day, including a weekend day.^25,75–78^ Non-wear (e.g., 60 minutes of ‘zero counts’) will be defined in accordance with previous research among older adults^75,78^ and people living with RA.^45^ Time spent in SB, LPA and MVPA will be determined using cut-points that have been validated in previous research with adults (e.g., Troiano et al.),^74^ and used in studies investigating SB and physical activity in the general population,^79^ in people with rheumatic diseases^80^ and in osteoarthritis.^81^

*ActivPAL3**^μTM^**.* The activPAL3^μTM^ posture sensor (9g; 2.35cm × 4.3cm × 0.5cm) will be initialised using activPAL3^μTM^ software and attached by the researcher to the front of the right thigh, in a mid-anterior position, with a waterproof, adhesive Tegaderm dressing. Participants will be asked to wear the activPAL3^μTM^ for 24 hours a day to enable assessment of time spent sitting/lying, standing and stepping, as well as sit-to-stand transitions.^82–85^ activPAL3^μTM^ software will be used to download the activPAL3^μTM^ data. Sleep time will be determined using self-reported information from the wear time logbooks and BAR, in conjunction with non-wear periods identified via algorithms applied to GT3X data. Specifically, the GT3X output generated by Actilife details at which time the participant removes (e.g., at bedtime) and replaces (e.g., at waking) the accelerometer throughout the 7-day period. This will be checked against the BAR, which details (over 3 days) when the participant woke up and went to bed.

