Participants will be required to have worn the activPAL3^μTM^ for ≥4 days, for ≥10 hours per day, including a weekend day, to be included in analyses.^76,86–88^ Variables derived for analyses will include: time spent sitting/lying, standing and stepping (i.e., hours per day), as well as the number of sit-to-stand transitions (i.e., sedentary breaks per day).

*Bouchard Physical Activity Record.* Participants will be asked to self-report the dominant activity undertaken every 15 minutes, over 3 days of the study week, including a weekend day (e.g., Thursday, Friday and Saturday).^66,89,90^ They will be asked to report this information in real-time, in order provide information regarding the context in which SB and physical activity were undertaken. For this study, the BAR has been adapted to include visual analogue scales, in which participants will be asked to report their average, minimum and maximum pain and fatigue on each of the 3 days. Specifically, at the end of each day, participants will be asked to mark a vertical line along a 100mm continuum from ‘no pain/fatigue’ to ‘extreme pain/fatigue’.

#### Visit 2

*Fasted blood sample.* Blood will be taken from the inside of the arm and collected in appropriate vacutainers. Standard laboratory procedures and Enzyme-Linked Immunosorbent Assays (ELISAs) will be used to measure: serum biomarkers of inflammation (i.e., TNF-α, IL-6, high-sensitivity CRP, ESR), plasma lipids (i.e., total cholesterol, high-density lipoprotein cholesterol, low-density lipoprotein cholesterol, triglycerides), plasma glucose and insulin.

*Disease activity score-28*. The number of swollen and tender joints in 28 joints of the body (i.e., hands, wrists, elbows, shoulders and knees) will be examined. Tenderness will be assessed via participants’ self-report when light pressure is applied to the joint by the researcher. The degree of swelling will be visually assessed and self-reported by the researcher. The number of swollen and tender joints will be used in conjunction with patients’ ESR and a self-reported degree of overall health ranging from 0 (very good) to 100 (very poor), to determine patients’ disease activity score-28 (DAS-28).^91^

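### The 5% ceiling on imputation runs the wrong way: it allows imputation where the method hardly matters and names none where it does

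*Protocol article*

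**What the plan says.** The protocol article has one provision on missing data, in Statistical Analyses: "Missing value analyses will be conducted via multiple imputation" or EM "methods in SPSS, where missing data does not exceed 5" per cent. It does not say whether the 5% counts items, variables or participants, when one method is preferred to the other, or what happens above 5%.

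Three other statements determine what the rule meets in practice:

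- **Longitudinal models (Statistical Analyses, Aim 1).** "regression models will examine if changes in objectively-assessed SB patterns significantly predict change in health outcomes". Each such model needs exposure and outcome at both time points. Aim 2 is built the same way, from determinants to behaviour.
- **Valid wear (Measures).** For the accelerometer, "For inclusion in analyses, participants will be required to have worn the GT3X for ≥4 days, for ≥10 hours per day", with a weekend day among them. The posture sensor has the same condition: "for ≥4 days, for ≥10 hours per day, including a weekend day, to be included in analyses". A recording that fails takes the participant out of the analyses.
- **Visits (Protocol).** "At each time point, participants will be asked to undertake 2 visits (i.e., visits 1 and 2) separated by a 7-day period". Most questionnaires and the physical assessments belong to Visit 1. The blood sample, DAS-28 and return of both devices belong to Visit 2. A participant can therefore have some 6-month data and lack the rest.

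**The concern.** Imputation is worth its assumptions when a material share of the data is missing and other recorded variables predict what is missing. With very little missing, any sensible method gives nearly the same answer. The printed rule licenses imputation in the second situation and withholds it in the first.

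Those affected are participants with partial 6-month data. Examples are a returned questionnaire set with an invalid device week, or a valid device week without a usable blood sample. A complete-case change model drops them, although their pain, fatigue, function and baseline activity are on record. If loss is related to symptoms, and symptoms are related to both sedentary behaviour and outcome, the remaining cases can give a biased slope as well as a less precise one.

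**Working it through.** **1. The plan's own figure.** Power Calculation gives n = 125 for high-sensitivity CRP, with power 0.80 and alpha .05. It prints no effect size, sidedness or number of predictors, so 125 cannot be reproduced, only solved backwards. For a two-sided correlation test with Fisher's z:

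r = tanh[(1.960 + 0.842)/√(125 − 3)] = tanh(0.2537) ≈ 0.248.

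**2. Power on complete cases, holding that r.** Power = Φ(0.2537·√(n − 3) − 1.960). The losses are assumed.

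| Loss | n left | Power |
|---|---|---|
| 0% | 125 | 0.80 |
| 5% | 118 | 0.78 |
| 10% | 112 | 0.75 |
| 20% | 100 | 0.70 |
| 30% | 87 | 0.64 |

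Within the range where the rule allows imputation, complete-case analysis costs about 2 points. The method can matter only beyond it.

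**3. What 5% could mean for a change model.** Four values are needed: exposure and outcome, each at two times. If each is 95% complete and losses are independent, the joint record is 0.95⁴ = 0.81 complete, so about 19% are lost. If all losses fall in the same people, the loss stays at 5%. The unit therefore decides whether the ceiling is met or broken by the same data.

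**4. Bias of complete cases.** Simulation with n = 125, true slope 0.25 and 2,000 replicates. Mean complete-case slope:

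| Loss | Random | Depends on exposure change | Depends on outcome change |
|---|---|---|---|
| 5% | 0.250 | 0.252 | 0.227 |
| 20% | 0.252 | 0.250 | 0.199 |
| 30% | 0.251 | 0.252 | 0.194 |

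There is bias only when loss depends on the outcome.

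**5. What multiple imputation recovers.**

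*Both change scores missing (6-month assessment missed entirely).* n = 125, true slope 0.25, loss driven by a baseline auxiliary, 20 imputations, Rubin's rules, 1,000 replicates:

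| Loss | Power, complete case | Power, multiple imputation |
|---|---|---|
| 10% | 0.76 | 0.76 |
| 20% | 0.68 | 0.68 |
| 30% | 0.64 | 0.63 |

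The standard deviation of the slope at 30% loss was 0.104 against 0.106. There is no gain.

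*Outcome missing, a 6-month auxiliary observed:*

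| Loss | Power, complete case | Power, multiple imputation |
|---|---|---|
| 20% | 0.65 | 0.72 |
| 30% | 0.59 | 0.67 |

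The gain is 7 to 8 points. Imputation also removed about 8% attenuation of the slope when loss depended on observed symptoms. The two simulations rest on different assumed parameters, so compare within a row only.

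**6. EM-completed data.** Predicted values treated as observed understate the standard error. Two simulation runs at n = 125 under the null (4,000 replicates) gave these type I errors at nominal 0.05:

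| Missing | Type I error |
|---|---|
| 5% | 0.057-0.064 |
| 10% | 0.080-0.084 |
| 20% | 0.119-0.126 |
| 30% | 0.175-0.181 |

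Only the first row lies within the present ceiling.

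**The case against.** The best defence is that the article never prescribes case deletion. It is silent above 5%, and a fuller protocol or analysis plan may hold the fallback. The 5% may also be meant only for unanswered questionnaire items, in which case it says nothing about dropout. Both points are fair: complete-case analysis above 5% is an inference for dropout, and exclusion is written down only for invalid wear. But a fallback elsewhere would have to override a ceiling printed here, and on the item-only reading invalid wear and missing blood samples have no imputation at all. Neither reading gives a reason for the ceiling.

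Four stronger readings are tempting, and the documents do not support them.

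- **That missingness is bound to exceed 5%.** No dropout or invalid-wear rate is given. The 0.95⁴ figure assumes independent losses, whereas missed visits tend to cluster in the same people, and not every model needs all four visits.
- **That the rule costs the study a large part of its power.** Assuming 10-30% dropout and 80-95% valid wear per wave leaves 125 × 0.9 × 0.95² ≈ 102 down to 125 × 0.7 × 0.8² = 56 complete cases, with power 0.71 down to 0.45. That is the cost of attrition. Step 5 shows that imputation does not win it back when both change scores are absent.
- **That the plan inflates type I error through EM to 0.08-0.18.** Those values arise at 10-30% missing, where the plan does not allow EM.
- **That complete-case slopes are necessarily biased.** Bias needs loss related to the outcome given the covariates. If it depends on unrecorded follow-up symptoms, standard imputation does not remove it either. Aim 2 already adjusts for 7-day pain and fatigue.

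**Conclusion.** The point stands in limited form, as a should-fix. The only printed missing-data rule has its condition reversed and its unit undefined. Followed as written, it most naturally drops partially observed participants from the change models once more than 5% is missing.

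The benefit of correcting it is modest: about 7 to 8 points of power at an assumed 20-30% missing outcome with a 6-month auxiliary on record, and removal of roughly 8% attenuation when loss depends on recorded symptoms. For those who miss the 6-month assessment entirely, the gain in power is close to nil. These sizes rest on assumed loss rates, assumed strength of the auxiliaries and missing-at-random given what is recorded. The direction of the error in the rule does not depend on them.

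**What to change.** In Statistical Analyses, delete the 5% ceiling and replace the sentence with the following:

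- **Primary handling.** Multiple imputation for all longitudinal models whatever the fraction missing, pooled by Rubin's rules. Auxiliaries are baseline and available 6-month pain, fatigue, DAS-28, Health Assessment Questionnaire score, sedentary behaviour and light activity. Use full-information maximum likelihood for the AMOS models.
- **EM.** Do not use EM-completed single data sets for inference. This becomes important once the ceiling is removed.
- **Invalid wear.** Reconcile the wear criteria in Measures with this rule by saying whether a failed recording makes the device variable missing or removes the participant.
- **Sensitivity.** Report complete-case results alongside.

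The cost is a few sentences and modest extra analysis in software the article already names, plus explicit reliance on missing-at-random. The change will not repair power lost to full dropout, which is a matter for recruitment and retention.
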